## Abstract

**Background:**

Physical activity (PA) is associated with positive cardio-metabolic health and emerging evidence suggests sedentary behavior (SB) may be detrimental to children's health independent of PA. The primary aim of the Transform-Us! study is to determine whether an 18-month, behavioral and environmental intervention in the school and family settings results in higher levels of PA and lower rates of SB among 8-9 year old children compared with usual practice (post-intervention and 12-months follow-up). The secondary aims are to determine the independent and combined effects of PA and SB on children's cardio-metabolic health risk factors; identify the factors that mediate the success of the intervention; and determine whether the intervention is cost-effective.

**Methods/design:**

A four-arm cluster-randomized controlled trial (RCT) with a 2 × 2 factorial design, with schools as the unit of randomization. Twenty schools will be allocated to one of four intervention groups, sedentary behavior (SB-I), physical activity (PA-I), combined SB and PA (SB+PA-I) or current practice control (C), which will be evaluated among approximately 600 children aged 8-9 years in school year 3 living in Melbourne, Australia. All children in year 3 at intervention schools in 2010 (8-9 years) will receive the intervention over an 18-month period with a maintenance 'booster' delivered in 2012 and children at all schools will be invited to participate in the evaluation assessments. To maximize the sample and to capture new students arriving at intervention and control schools, recruitment will be on-going up to the post-intervention time point. Primary outcomes are time spent sitting and in PA assessed via accelerometers and inclinometers and survey.

**Discussion:**

To our knowledge, Transform-Us! is the first RCT to examine the effectiveness of intervention strategies for reducing children's overall sedentary time, promoting PA and optimizing health outcomes. The integration of consistent strategies and messages to children from teachers and parents in both school and family settings is a critical component of this study, and if shown to be effective, may have a significant impact on educational policies as well as on pedagogical and parenting practices.

**Trial registration:**

ACTRN12609000715279; Current Controlled Trials ISRCTN83725066

## Background

In the past few decades, rates of overweight and obesity and related metabolic and cardiovascular risk factors in children have steadily increased worldwide [1-4]. Physical activity plays an important role in the prevention of metabolic and cardiovascular health risk factors in children [5]. Increasingly, evidence suggests that sedentary behaviors, such as prolonged periods of television viewing, electronic games, and computer use (collectively called screen-time) may adversely affect children's weight status, independent of physical activity participation [6,7]. While these screen behaviors are most commonly performed during children's leisure-time there are many opportunities throughout the day for children to be sedentary (e.g., being driven to school, sitting in class, and sedentary homework). Further, while some longitudinal evidence suggests that increases in the time children spend in sedentary behaviors seem to be off-set by corresponding decreases in physical activity during the primary school years [8], other studies have reported independent changes in these behaviors over time suggesting that they should be viewed as separate rather than converse constructs [9].

There is emerging evidence that not just screen time, but total sedentary time may be detrimental to children's health. A cross-sectional study of 208 Portuguese children (mean age 9.8 years) found positive associations between accelerometer-measured sedentary time (defined as < 500 Actigraph counts per minute [cpm]) and insulin resistance, and inverse associations between moderate- to vigorous-intensity physical activity (MVPA; ≥2, 000 cpm) and insulin resistance [10]. A study of 111 US children (aged 3-8 years), however, found no cross-sectional associations between time spent sedentary (< 100 cpm) and systolic or diastolic blood pressure (BP) [11]. Nevertheless, that study reported that children in the highest tertile for proxy-reported television viewing time (approximately 155 mins/day) were significantly more likely to have higher systolic and diastolic BP compared with children in the lowest tertile (approximately 8 mins/day).

Observational evidence from studies among adults suggests that the manner in which time spent sedentary is accumulated may also be detrimental to health. For example, a cross-sectional study with 168 Australian adults (mean age 53 years) found that independent of MVPA levels, those with less frequent interruptions to accelerometer-measured sedentary time (≥100 cpm) with light-intensity physical activity had less favourable health profiles (waist circumference, body mass index, triglycerides, 2-hour plasma glucose) compared to those with more frequent interruptions [12]. Interestingly, the average duration of light-intensity breaks was less than five minutes, suggesting that even brief interruptions to time spent sedentary may be beneficial to health. To our knowledge, no observational or experimental studies have examined the association of interruptions to sedentary or sitting time and health in children, nor has the role of light-intensity physical activity and children's health been previously studied.

While few intervention studies have examined the effectiveness of strategies to reduce children's overall sedentary time, several review papers have summarized the effectiveness of interventions to reduce children's screen time [6,13,14]. While this evidence suggests these strategies (delivered primarily through school-based curriculum), have positive effects on children's weight and have successfully reduced TV viewing, as noted earlier, there are many opportunities to be active throughout the day both at school and at home [15] and few if any of these interventions to reduce children's screen time have resulted in corresponding increases in physical activity.

Several studies have reported significant positive effects on children's physical activity in the school setting by targeting the school curriculum or through changes in the school environment [16-19]; however, few studies report on intervention effects on children's sedentary time. A recent experimental study by Benden et al. among children in four classes in Central Texas introduced standing desks into classrooms and found that after 12 weeks all children were standing for 75% of the time [17]. However, the intervention only targeted energy expenditure at school and did not incorporate strategies to increase energy expenditure or reduce sedentary behavior outside of school hours. A further challenge with this type of intervention is whether the aim is to reduce children's sedentary time, increase physical activity or both. In a meta-analysis of intervention studies that aimed to promote young people's physical activity or reduce screen time, pooled effect sizes of 0.12 and -0.29 respectively were reported [14]. The authors concluded that strategies to reduce sedentary behavior appeared to be more effective than strategies to increase physical activity. However, the efficacy of strategies to increase physical activity and reduce sedentary behavior separately and in combination has not been examined.

Ecological models suggest that settings-based approaches may be an effective method for intervening with children's health behaviors [20,21]. Interventions that target places and contexts in which large numbers of children are sedentary or active are likely to have a greater public health impact than approaches that involve one-on-one program delivery. In addition, an important aspect in the development of effective and efficacious behavioral interventions is the use of a theoretical framework [22,23]. The use of behavioral theory helps guide the development of strategies that are most likely to result in changes in behavior through targeting the key mechanisms or mediating constructs of change [24,25]. Commonly employed theories in children's physical activity and sedentary behavior intervention studies include: social cognitive theory [26]; theory of planned behavior [27]; and behavioral choice theory [28]. A limitation of many of these theories is the focus on intrapersonal factors, which on the one hand are important for targeting change at the individual level, but are less useful when targeting changes at the population level. More recently, but less frequently, ecological models such as the social ecological model of health promotion [29] and the family-based ecological systems theory [20] have also been employed in interventions to promote children's physical activity with mixed success [30,31].

Very few studies, even those that report use of behavioral theory in the design of their intervention, examine the mediators or mechanisms of behavior change. Several reviews of mediators of physical activity interventions in children and youth have identified key mediators to target including: self-efficacy; behavioral capability; perceived social support; physical activity knowledge and beliefs; and enjoyment of or preference for physical activity [32-34]. Just two studies have examined possible mediators of change in sedentary behaviors such as television viewing and computer use in young people [35,36]. The DOiT study was an obesity prevention intervention based on the theory of planned behavior and habit strength theory [37] that aimed to improve dietary and physical activity habits as well as reduce sedentary time of Dutch adolescents [35]. In that study there were no mediating effects of attitude, subjective norms (i.e. the degree to which an individual is inclined to agree with the expectation of other important persons' opinions, normative beliefs), behavioral control or habit strength on youth screen time. Based on the self-determination theory [38] and the theory of meanings of behavior [39], the Get Moving! program was a media-based intervention delivered via the school setting that aimed to increase physical activity and decrease sedentary behaviors in predominantly Latino middle school girls in California, USA [36]. The authors found a non-significant trend for a mediating effect of intrinsic motivation to be physically active on television viewing time. No other mediating effects were observed.

It is therefore important that intervention studies not only target key mediators that lie on the behavior change pathway, but that these pathways are then tested statistically. This will ensure a better understanding of why an intervention worked or not and will further inform the utility of behavior change theories. Another often-overlooked aspect of children's health behavior change interventions is the economic cost of program delivery. Not only is it important to test whether an intervention works and why, it is also critical that it is cost effective. Cost-effectiveness analysis combines effectiveness and cost data to show whether an intervention represents 'value for money', with results expressed as incremental cost-effectiveness ratios. A range of standard methods are available to guide economic evaluation of an intervention program [40,41]. For example, the Assessing Cost Effectiveness (ACE)-Obesity study examined the economic evaluation of thirteen interventions which targeted unhealthy weight gain in children and adolescents [42,43]. While the cost-effectiveness of interventions varied greatly, the most cost-effective strategies included 'Reduction of TV advertising of high fat and/or high sugar foods and drinks to children', 'Laparoscopic adjustable gastric banding' and the 'multi-faceted school-based programme with an active physical education component'[42]. Further research is required to identify the cost-effectiveness of strategies to reduce children's sedentary behavior and promote physical activity in the school and home settings.

This proposal builds on our program of research [42,44,45] aimed at identifying effective and cost-effective strategies that positively influence children's health behavior and translate to improved health outcomes. This paper presents a summary of the Transform-Us! intervention including its aims, development, intervention methods and assessment protocols.

### Aims

The primary aim of the Transform-Us! study is to determine whether an 18-month, behavioral and environmental intervention in the school and family settings results in higher levels of physical activity and lower rates of sedentary behavior among 8-9 year old children compared with usual practice (post-intervention and 12-months follow-up). The secondary aims are to determine the independent and combined effects of PA and SB on children's cardio-metabolic health risk factors; identify the factors that mediate the success of the intervention; and determine whether the intervention is cost-effective.

### Study Protocol Overview

Transform-Us! is a four-arm cluster randomized controlled trial with primary schools in Melbourne, Australia being the unit of randomization. The intervention will run for approximately 18 months (end of Term 2, 2010 to end of Term 4, 2011), with a 12-month tapered maintenance period in 2012. Transform-Us! is funded by a National Health and Medical Research Council Grant (No.533815). Ethical approval was obtained from the Deakin University Human Research Ethics Committee (EC 141-2009), the Victorian Department of Education and Early Childhood Development (2009_000344) and the Catholic Education Office (Project Number 1545).

## Methods/Design

### Study population

Twenty primary schools within a 50 km radius of Melbourne will be involved in Transform-Us!. All year 3 children in the intervention schools will receive the program and all year 3 children in all schools will be invited to participate in the evaluation of the intervention with the aim to recruit 600 students. Due to significant increases in sedentary behaviors and declines in physical activity among children in primary school, 8-9 year olds were considered a key target population. In addition, for practical purposes a three-year study implemented in year 3 would ensure children remained at primary school throughout the entire study ensuring ease of follow-up.

### Recruitment of schools

School principals will be contacted via fax or email and invited to participate in the Transform-Us! study. All interested principals (and teachers if in attendance) will be given a detailed presentation outlining the program and required commitment. Principals who agree to participate in the study will then be provided with a plain language statement and consent form to be signed and returned prior to participation. As the Transform-Us! program will involve modification to the delivery of the school curriculum, approval from the school council/board will also be required.

### Recruitment of participants

All year 3 children in eligible schools will be provided with an information pack for their parents or carers/guardians (hereafter referred to as parents) containing a plain language statement and consent form for the parents' and child's participation. As the school will have consented to the program being delivered to all year 3 children and parents, consent will only be required for the evaluation components. Parents will be able to nominate which assessment components they give consent for their child to participate in (i.e., accelerometer, inclinometer, anthropometry, survey, blood pressure and/or blood sample, or all components). At baseline, all year 3 teachers will be provided with an information pack containing a plain language statement and consent form to be signed and returned prior to participation in the evaluation assessments. To maximize the sample and to capture new students arriving at intervention schools, recruitment will be on-going up to the post-intervention time point. The schools, teachers and participants will not be paid to participate in Transform-Us!.

### Sample size calculations

It is expected that the intervention effects on behavioral and biological primary outcomes will be moderate in size (standardized difference ~ 0.32, equivalent to a mean change in objectively-measured PA of 8 minutes per day [SD = 18 min] and a change in body mass index (BMI) units (age-sex difference from population norm data) of 1.9 kg/m^2 ^[SD = 0.25]) [25,46]. Without accounting for school cluster effects, the number of participants needed to detect a standardized difference of 0.32 with 0.8 power for sedentary behavior (SB-I) and physical activity (PA-I) alone and in combination (SB+PA-I), using a significance level of 0.05 with a two-tailed test, assuming a retention rate of 91% (based on the team's previous experience) and 20 participating schools, would be 340 in total (17 per school). With a previously observed school clustering effect of 0.018 (intra-class correlations [ICCs] for sedentary behavior, physical activity and BMI outcomes estimated using data from a previous intervention study)[44], the minimal total number of participants needed is 520, i.e., 26 per school. Hence, we will conservatively recruit 30 participants per school, giving a total sample size of 600 participants.

Moderate mediated effects of the intervention on the behavioral outcomes are expected (here a moderate mediated effect size is defined as standardized regression coefficients α and β of ~ 0.39)[47]. According to a 2007 simulation study by Fritz and MacKinnon [48], to detect a moderate mediated effect size with 0.8 power, using a significance level of 0.05 with a two-tailed test and bias-corrected bootstrap methods, ~ 61 independent observations are needed. If we assume a 9% rate of loss to follow-up, an average school cluster effect of 0.03 for the mediators (ICCs estimated using data from a previous intervention study)[44] and an average of 30 observations per school (see above), the sample size needed to detect a moderate mediated effect size would be 100 (20 per school). Hence, the sample size needed to detect moderate intervention effect sizes with 0.8 power for the primary outcomes (n = 600) will also be sufficient to detect a moderate-sized effect with 0.8 power for the mediating variables.

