### Combined sedentary behavior and physical activity intervention arm (SB+PA-I)

Schools randomized to the combined SB+PA-I intervention arm will receive a blended version of the two interventions, but with the same intervention 'dose'. For example, when children in this arm complete a behavioral contract to switch off the television, they will be encouraged to participate in physical activity (SB-I children will not be directly encouraged to participate in activity when they switch off their television). The combined intervention arm will include 18 class lessons (9 per year), standing lessons and interruptions to children's classroom sitting time (short breaks), the promotion of physical activity during recess and lunch breaks, and 18 newsletters to parents.

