### Data analysis

All statistical analyses will be performed using Stata 9.1 for Windows (StataCorp LP) and will adjust for clustering by observations by school (the unit of randomization). All analyses will be conducted using the intention to treat principle. Generalized Estimating Equations (GEE) [84] will be used to fit regression models to describe the effects of the intervention on key outcome variables among children. Separate models will be fitted to determine differences in key outcome variables in the intervention and control groups.

Separate models will be evaluated for each assessment point (mid-intervention; post-intervention; 12 months follow-up), adjusting for baseline levels of the outcome, and, where appropriate, baseline levels of the mediating variables. PA-I and SB-I intervention conditions will be the predictors of primary interest (entered in the form of two indicator variables and their interaction term). Analyses will be performed excluding and including children who were recruited to the study after baseline. For physical activity outcomes, we will compare the PA-I and SB+PA-I versus the SB-I and C groups. For sedentary behavior outcomes, we will compare SB-I and SB+PA-I versus the PA-I and C groups. For health outcomes, we will compare C versus the other three groups and the SB+PA-I versus the single intervention groups. All models will be adjusted for measured confounders. As it has been argued that adjustment for multiple comparisons should not be used when assessing evidence about specific hypotheses no adjustment for multiple comparisons will be performed [85]. To evaluate the magnitude and direction of the intervention effects mediated by intrapersonal, interpersonal and environmental processes, the product-of-coefficient method will be used [86]. A first set of GEE regression models will assess the impact of the intervention condition (regression coefficient α) on the residualized change score of the hypothesized mediators (Table 1), after controlling for significant covariates. A second set of GEE regression models will estimate the independent effects of the intervention condition and residualized changes in the mediators (regression coefficient β) on changes in the outcome variables. The significance of the product of the regression coefficients α and β (representing the mediated effect of the intervention) will be tested using bias-corrected bootstrap methods as outlined by Pituch and colleagues [87].

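### The 0.8 power claimed for the single and combined arms is the power of one comparison of 10 against 10 schools; arm-versus-control and health-outcome contrasts fall below it

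*Protocol article*

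**What the plan says.** **Sample size calculations.** The target is "to detect a standardized difference of 0.32 with 0.8 power for sedentary behavior (SB-I) and physical activity (PA-I) alone and in combination (SB+PA-I"). The test is two-sided at 0.05, and 91% retention and 20 schools are assumed. Before any allowance for clustering, the number "would be 340 in total (17 per school"). Allowing for an ICC of 0.018, taken from earlier data, raises it to 520 (26 per school), and 600 (30 per school) will be recruited. The section opens by applying the effect size of about 0.32 to behavioural and biological outcomes alike, with BMI as the biological example.

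**Data analysis.** The PA-I and SB-I conditions are the predictors of main interest, "entered in the form of two indicator variables and their interaction term". The comparisons are then named. "For physical activity outcomes, we will compare the PA-I and SB+PA-I versus the SB-I and C groups", and sedentary outcomes use the mirror-image pooling. Health outcomes use control against the other three arms, and the combined arm against the two single arms.

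**Combined arm.** It receives "a blended version of the two interventions, but with the same intervention 'dose"'.

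**The concern.** SB-I, PA-I and SB+PA-I are the article's labels for randomized arms, and the aim is framed against usual practice. The power sentence therefore reads naturally as promising 0.8 for each arm against control. Such a comparison uses 5 against 5 schools, half the trial. A calculation that uses all 20 schools in one two-group comparison cannot deliver it.

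The health contrasts raise the same problem whatever the model coding. The power statement extends to BMI, yet the Data analysis section assigns health outcomes to splits of 5 against 15 and 5 against 10 schools, which are less efficient than 10 against 10.

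The model description adds an ambiguity. If the indicators are coded 0/1 and the product term is present, the raw PA coefficient estimates PA-I against control alone, not the pooled contrast named a few lines later.

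At stake is interpretation. A null arm-versus-control result, or a null health result, could be read as evidence of no effect from a trial believed to have 0.8 power for it.

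**Working it through.** **Inputs.** From Sample size calculations: two-sided alpha 0.05, power 0.8, d = 0.32, retention 0.91, ICC 0.018, 30 recruited in each of 20 schools. Five schools per arm is an assumption (20/4).

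**The plan's own figures.**

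- Per group: 2 × (1.96 + 0.8416)² / 0.32² = 153.3, rounded up to 154.
- Two groups: 2 × 153.3 / 0.91 = 337, or 2 × 154 / 0.91 = 338.5. The plan has 340.
- Design effect at 30 per school: 1 + 29 × 0.018 = 1.522. Then 340 × 1.522 = 517, which at 26 per school becomes 520.

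Both figures reproduce as one comparison of two halves of the sample. Sizing each arm against control would have started from 4 × 154 / 0.91 = 677 before clustering.

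**Power at 600 recruited.**

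- Retained per school: 30 × 0.91 = 27.3.
- Design effect: 1 + 26.3 × 0.018 = 1.473.
- Effective children per school: 27.3 / 1.473 = 18.53.
- SE = √(c / 18.53), in SD units, where c depends on how many schools stand on each side.
- Normal power = Φ(0.32 / SE − 1.96). The t version uses the noncentral t with 20 − 4 = 16 df.

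| Contrast | c | SE | Normal | t, 16 df |
|---|---|---|---|---|
| Pooled PA or SB, 10 v 10 | 1/10 + 1/10 = 0.200 | 0.104 | 0.87 | 0.82 |
| Each arm v control, 5 v 5 | 1/5 + 1/5 = 0.400 | 0.147 | 0.59 | 0.53 |
| Control v other three, 5 v 15 | 1/5 + 1/15 = 0.267 | 0.120 | 0.76 | 0.71 |
| SB+PA-I v single arms, 5 v 10 | 1/5 + 1/10 = 0.300 | 0.127 | 0.71 | 0.66 |
| Interaction of 0.32 | 4 × 1/5 = 0.800 | 0.208 | 0.34 | 0.30 |

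At the stated minimum of 520 (23.7 retained per school), arm against control has 0.55 / 0.50.

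**What 0.8 for arm against control would take with 20 schools.** Solve 5m / (1 + (m − 1) × 0.018) = 154 for m. This gives m = 154 × 0.982 / (5 − 154 × 0.018) = 67.9 retained per school, or 74.6 recruited, about 1,490 in total (normal approximation). Doubling 520 would not be enough, because the design effect grows with the number of children per school.

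**The model.** Write the mean as b0 + b1·PA + b2·SB + b3·PA·SB with 0/1 indicators. Then b1 is PA-I minus control (SE 0.147). The pooled PA contrast is the average of b1 and b1 + b3, that is b1 + b3/2 (SE 0.104). The two agree only if b3 = 0. With −1/2, +1/2 coding, the PA coefficient is the pooled contrast itself.

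**The case against.** The strongest reply is that the Data analysis section does name the pooled contrasts for physical activity and sedentary outcomes. These use all 20 schools and have 0.82 to 0.87 power. The two-indicator-plus-interaction model has one parameter per arm, so the pooled contrasts can be estimated from it under any coding, with no further loss of power in a balanced design. Nothing says that the indicators are coded 0/1 or that tests will be read off raw coefficients, and such detail is often left to an analysis plan. This stands. A reader might infer that the primary analysis itself has only 0.53 to 0.59 power; the document does not support that. The harm arises only if 0/1 coefficients are taken as the main effects.

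A reader might also infer from the matched dose of the combined arm that an interaction is likely. The document gives no figure for one. The combined arm keeps the standing lessons and short breaks of SB-I, and the equipment, line markings, signage and pedometers of PA-I. What is visibly blended is mainly lessons, homework and newsletters. A non-zero interaction is a possibility, no more.

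Two further points soften the power figures without removing the error:

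- **Baseline adjustment** is planned and could raise power. If variance falls by 1 − r², arm against control reaches 0.8 (normal) when 1 − r² = (2.178 / 2.8016)² = 0.604, so r is about 0.63. The document gives no such correlation, and its 340 and 520 take no credit for one.
- **The raw example** of 8 minutes with SD 18 is d = 0.44, not 0.32. At 0.44, arm against control would have about 0.81 (t) to 0.86 (normal). That is a separate inconsistency; 340 and 520 rest on 0.32.

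Neither point rescues the power sentence as written.

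**Conclusion.** The power statement is wrong as written. On the plan's own inputs, 0.8 or better at d = 0.32 with 600 recruited holds for the two pooled factorial contrasts. It does not hold for single or combined arms against control, for the two health contrasts, or for the interaction. The gap is largest for arm against control, at 0.53 to 0.59. The health contrasts fall short by less, at 0.66 to 0.76, but that shortfall does not depend on model coding.

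The figures assume five schools per arm, equal school sizes, the stated ICC and retention, and no gain from baseline adjustment. The model wording is an ambiguity to close, not a demonstrated error. The point should be fixed, but it does not threaten the design, because the contrasts named for the behavioural outcomes are adequately powered.

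**What to change.** **Sample size calculations.** State that 0.8 power applies to the two pooled factorial contrasts only. Give the lower power for each arm against control, for the two health contrasts and for the interaction, with the assumptions behind them.

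**Data analysis.** State that the primary tests for physical activity and sedentary outcomes are the pooled contrasts already listed, obtained either by −1/2, +1/2 coding or as marginal contrasts from the model. Say explicitly that they are not the raw 0/1 coefficients, which estimate a single arm against control when the product term is present. Report the interaction and the arm-versus-control effects as secondary, with confidence intervals.

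**Cost.** A few sentences in two sections. No extra schools or children and no new data are needed. Some published power figures become less favourable.

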##### *activ*PAL™ inclinometer

A sub-sample of randomly selected children will concurrently wear a PAL Technologies Ltd, Glasgow, Scotland http://www.paltech.plus.com/products.htm inclinometer *activ*PAL™. The *activ*PAL™ is a small device (5 × 3.5 × 0.7 cm) weighing 20 g and is worn on a garter belt positioned at the mid-anterior aspect of the right thigh during waking hours (apart from water-based activities) for eight days at each of the measurement points. The following parameters will be calculated from this device: sedentary time (sitting/lying time); stand time (not walking); walk time; and sit-to-stand events. The device has been found to have acceptable validity in assessing these parameters in adults [64,65].

ActiGraph and *activ*PAL™ data validity criteria will be assessed prior to inclusion in analysis. A minimum of four valid days, including one weekend day will be required. To be included in analyses, a day will be considered valid if the child has at least eight hours of wear time per day or at least 50% wear time within periods of the day (e.g., classtime). Further, 20 minutes of consecutive zeros will be considered non-wear time. Recordings of over 16000 counts per minute (cpm) will be excluded as it indicates unit malfunction.

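### The 0.8 power claimed for the primary outcomes at n = 600 is not established for inclinometer sitting time, which is measured only in a random sub-sample of unstated size

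*Protocol article*

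**What the plan says.** The abstract's Methods/design paragraph names the instruments for the primary outcomes: "Primary outcomes are time spent sitting and in PA assessed via accelerometers and inclinometers and survey". In the body, the inclinometer subsection stands under the Primary outcomes heading, and its first parameter is sitting/lying time. The same subsection restricts who is measured: "A sub-sample of randomly selected children will concurrently wear a PAL Technologies Ltd". It gives no number. Under Recruitment of participants, parents may also consent to some assessments and decline others, the inclinometer among them.

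Sample size calculations starts from "the number of participants needed to detect a standardized difference of 0.32 with 0.8 power", "using a significance level of 0.05 with a two-tailed test", and "assuming a retention rate of 91% (based on the team's previous experience) and 20 participating schools, would be 340 in total (17 per school"). The next step begins "With a previously observed school clustering effect of 0.018" and arrives at 520, which is rounded up to 600 (30 per school). The section closes by describing "the sample size needed to detect moderate intervention effect sizes with 0.8 power for the primary outcomes (n = 600") as also sufficient for the mediators. It makes no exception or separate calculation for an outcome measured on fewer children.

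Data analysis sets the contrast for sedentary outcomes as the two arms with a sedentary component against the two without, adjusted for the baseline value.

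**The concern.** Three statements do not fit together: inclinometer sitting time is a primary outcome, it is measured in a sub-sample, and the primary outcomes have 0.8 power on 600 children. An outcome measured on part of the sample cannot take its power from the whole sample.

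Reducing sedentary behaviour is half of the primary aim, and the inclinometer is the device that records sitting and lying as such. A non-significant inclinometer result, reported as a primary outcome of a trial said to have 0.8 power, could be read as evidence that the programme does not reduce sitting. The comparison may have had much less power than that.

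**Working it through.** **Inputs from Sample size calculations:** d = 0.32; two-sided 0.05; power 0.8; retention 91%; 20 schools; ICC 0.018; 30 recruited per school. From Data analysis: two arms against two arms, taken as 10 versus 10 schools (equal arms assumed, the most favourable case).

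**1. Reproduce the plan.**
- Total without clustering: 4 × (1.96 + 0.8416)² / 0.32² = 306.6. Divided by 0.91 this is 336.9 (plan: 340, or 17 per school).
- Design effect at 30 per school: 1 + 29 × 0.018 = 1.522. Then 340 × 1.522 = 517.5, or 26 per school × 20 = 520 (plan: 520).

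Both printed figures reproduce, so d = 0.32 with this contrast is what generates them.

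**2. Power by number of wearers.** The article gives no sub-sample size, so the sizes below are assumed. With r enrolled wearers per school, m = 0.91r are analysed, DE = 1 + (m − 1) × 0.018, n_eff = 20m / DE, and power = Φ(0.32 × √(n_eff/4) − 1.96). The detectable difference at 0.8 power is 2.8016 / √(n_eff/4).

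| Wearers enrolled | m | DE | n_eff | Power at 0.32 | Detectable d |
|---|---|---|---|---|---|
| 100 | 4.55 | 1.064 | 85.5 | 0.316 | 0.61 |
| 200 | 9.10 | 1.146 | 158.8 | 0.523 | 0.44 |
| 300 | 13.65 | 1.228 | 222.4 | 0.665 | 0.38 |
| 400 | 18.20 | 1.310 | 277.9 | 0.760 | 0.34 |
| 600 | 27.30 | 1.473 | 370.6 | 0.869 | 0.29 |

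**3. Break-even for 0.8 power at d = 0.32.** Solving 20m / (0.982 + 0.018m) = 306.6 gives m = 20.8, r = 22.9, about 457 children (457/600 = 76%). Other reasonable choices move this figure:
- Enrolled rather than analysed cluster size in the design effect: 475.
- The plan's fixed design effect of 1.522: 336.9 × 1.522 = 513, or 520 with the plan's rounding.
- A t reference on 18 df in place of the normal: 536 (power 0.480 at 200, 0.617 at 300, 0.713 at 400).
- Baseline adjustment removing 25% of the variance (assumed; a baseline correlation of 0.5), with the ICC unchanged: required n_eff = 0.75 × 306.6 = 230, so m = 14.2 and about 313 children.
- The plan's own minutes in place of 0.32. It gives "standardized difference ~ 0.32, equivalent to a mean change in objectively-measured PA of 8 minutes per day [SD = 18 min", but 8/18 = 0.44. Required n_eff = 4 × 7.849 / 0.4444² = 159, so m = 9.1 and about 200 children.

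**4. A check without any clustering.** The plan needs 340 children at d = 0.32 before clustering is considered. Without baseline adjustment, a sub-sample below about that number falls short even at an ICC of zero.

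**The case against.** The strongest reply has four parts.

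- **The sub-sample size is unknown.** A journal article may leave it to the full protocol, and about 457 or more wearers would keep 0.8 on the main calculation. This stands, and it makes any shortfall conditional. It does not rescue the statement as printed, because a fuller document giving the number would still not make 600 the sample for this outcome.
- **The calculation was not built on the inclinometer.** It is expressed in objectively measured activity and BMI, and the sentence at issue is a closing remark about mediators. The accelerometer also measures sedentary time, with no sub-sampling stated, and the inclinometer is worn alongside it. This also stands: the n = 600 basis can hold for accelerometer sedentary time. But the closing sentence covers the primary outcomes without distinction, and the outcome list includes the inclinometer.
- **The threshold is not unique.** Correct. It runs from about 200 to 536 depending on effect size, baseline adjustment and reference distribution, so no single cut-off should be attributed to the plan. The lowest value uses an 8/18 ratio that describes physical activity, not sitting, and that does not generate the plan's 340 or 520.
- **Low power does not disqualify a primary outcome.** Agreed. Whether the inclinometer stays primary is a design choice that this point does not touch.

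A reader might infer that 0.8 power is simply false for the inclinometer, or that the comparison is known to be underpowered. The document does not support either inference, because it gives no sub-sample size and no effect size, SD or ICC specific to inclinometer sitting time.

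**Conclusion.** The printed arithmetic is sound for outcomes measured on all children. What fails is the scope of the power statement: n = 600 is not the sample for inclinometer sitting time, so 0.8 power is not established for it.

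The size of any shortfall depends on the sub-sample. At d = 0.32 without baseline adjustment, power is below 0.8 with fewer than roughly 457 to 520 wearers (normal approximation). It is close to even odds at 200 and about two in three at 300. Under the kinder assumptions above, about 313 or about 200 would be enough. All of this assumes that the plan's effect size, ICC and 91% retention carry over to the inclinometer measure, and that schools split 10 versus 10. Partial consent and the valid-day rule could only reduce the analysed number further.

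The statement should be corrected, since it misdescribes a property of a listed primary outcome. It does not call the trial's sample size into question.

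**What to change.** In Sample size calculations, limit the 0.8 power statement to primary outcomes measured on all 600 children. Add the planned inclinometer sub-sample size, with its own power at 0.32 or its detectable standardized difference. For illustration, if 200 children were sub-sampled, the text would give a detectable difference of about 0.44 at 0.8 power. A reader can then judge a null inclinometer result against the power it really had.

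The cost is one or two sentences and one calculation. No change to the number of children or devices is needed, and inclinometer sitting time need not lose primary status. The downside is a less favourable stated power for that outcome, unless the planned sub-sample proves large enough.
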